### Primary outcomes

• Health status; measured using the WOMAC Osteoarthritis Index for OA of the knee (WOMAC LK3.0). Also self-administered, the WOMAC assesses pain, stiffness and physical function [13] and can be completed in less than 5 minutes. Two major studies have shown WOMAC pain, stiffness and physical function subscales are valid and the questionnaire is reliable and sensitive enough to detect changes in health status following a variety of interventions [14,15]

• Quality of life; measured using the Short Form 36v1 (SF-36) questionnaire. This 36 item questionnaire is self administered, and can be completed in about 15 minutes [16]. Scores for 8 sub components reflecting both physical and mental status can be generated. Reliability and validity have been established in numerous studies [16,17].

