### Statistical Power Calculation

A priori power calculations for this study will be based on the quality of life outcome as measured by the SF-36. Sample size was calculated according to guidelines in the SF-36 Users Manual to determine differences in changes over time between the intervention and control groups using a repeated measures design allowing an inter temporal correlation between scores of 0.60 [16]. The pilot study SF-36 data showed an average improvement of 10 points across the eight domains measured. Assuming this level of improvement is achieved in the intervention group and there is no change in the control group and allowing for a 10% drop out rate, the number of participants required per group will be 60 [16]. In the pilot study, there was a drop out rate of 5% over 3 years, so allowing 10% is a conservative estimate. Differences in changes in functional ability measured using the WOMAC, similar in magnitude to those previously documented [24] would also be detectable in a sample of this size.

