### Data Analysis

Data will be analyzed in a blinded manner. Treatment groups will be examined for comparability at baseline. Main comparisons between treatment groups will be performed using an intention to treat analysis. To test the effects of treatment, between group differences in changes over time will be examined using repeated measures ANOVA. Separate analysis will be conducted for each outcome variable. Statistical significance will be inferred at a 2-tailed p < 0.05. Results will not be adjusted for multiple comparisons as all outcomes of interest have been nominated a priori and such adjustment would likely render all findings of interest, despite their clinical importance, non-significant.

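### Two whole questionnaires are primary, each score is tested at 0.05 without adjustment, and neither reason given for not adjusting is valid

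*Protocol article*

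**What the plan says.** Under Primary outcomes, the protocol article lists two instruments. For the first it says that "the WOMAC assesses pain, stiffness and physical function". For the second it says: "Scores for 8 sub components reflecting both physical and mental status can be generated". It selects no total, summary score, subscale or domain as decisive. The Abstract gives assessments at baseline, 8 weeks and 6 months, and no follow-up time is named as primary.

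Under Data Analysis, the test is a repeated measures ANOVA of between-group differences in change, applied outcome by outcome: "Separate analysis will be conducted for each outcome variable". The threshold is fixed: "Statistical significance will be inferred at a 2-tailed p < 0.05". Adjustment is then declined on two grounds. The first is prior nomination: "Results will not be adjusted for multiple comparisons as all outcomes of interest have been nominated a priori". The second is that "such adjustment would likely render all findings of interest, despite their clinical importance, non-significant".

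The article states no hierarchy, no gatekeeping, and no rule on how many scores must succeed.

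**The concern.** The article takes an explicit decision on multiplicity and argues for it, so this is not a detail left to an unseen analysis plan. Both arguments fail.

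- **Prior nomination.** Pre-specification stops outcomes being chosen after the data are seen. It does nothing to the probability that at least one of several pre-specified tests is falsely positive.
- **Loss of significance.** That a stricter criterion might not be met is a reason to choose fewer primary scores or a larger sample. It is not a reason to leave the error rate uncontrolled.

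The Hypothesis section covers quality of life, knee function and pain, and the Discussion says that the results are to guide clinicians and funding bodies. With no decisive score and no success rule, the error rate attached to a claim of effectiveness is undefined, and it may be well above the stated 5%.

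**Working it through.** **Inputs from the protocol article.** Two-tailed 0.05 per outcome, separate analyses, no adjustment (Data Analysis). 3 WOMAC subscales and 8 SF-36 components (Primary outcomes). 60 per group including 10% dropout, a 10-point average SF-36 improvement, and a correlation over time of 0.60 (Statistical Power Calculation). 146 recruited (Subjects).

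**Assumptions.** All 11 scores are tested (3 + 8 = 11; the article does not list the tests). Test statistics are equally correlated normals with correlation r from 0 to 0.8. Power is 80% per score at 0.05. Allocation is 1:1. The article gives none of these.

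**The plan's own figure.** No family-wise error rate is stated. The 60 per group cannot be reproduced, because neither power nor SD is given. It can only be back-solved: 54 evaluable / 0.9 = 60. At 80% power, 54 per group implies an SD of change of 10 × √(54/2) / (1.960 + 0.842) = 18.5. With a correlation of 0.60 the raw SD is 18.5 / √(2 × 0.4) = 20.7. At 90% power the corresponding values are 16.0 and 17.9.

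**Step 1: false-positive rate.** Under independence:

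- at least one false positive in either direction: 1 − 0.95^11 = 0.431
- at least one in the program's favour: 1 − 0.975^11 = 0.243

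Simulation with 400,000 draws gives, for 11 scores:

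| Assumed r | Either direction | In the program's favour |
|---|---|---|
| 0 | 43% | 24% |
| 0.3 | 37% | 19% |
| 0.5 | 30% | 15% |
| 0.7 | 22% | 11% |
| 0.8 | 18% | 9% |

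The nominal rates for a single test are 5% and 2.5%.

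On the most lenient reading, one score per instrument, the rates under independence are 1 − 0.95² = 9.75% in either direction and 1 − 0.975² = 4.9% in the program's favour.

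**Step 2: would adjustment remove all findings?** At 80% power the expected test statistic is 1.960 + 0.842 = 2.80. The Bonferroni threshold over 11 is 0.05/11 = 0.0045, a critical value of 2.84. Power per score is then 49%. Holm rejects at least one score exactly when Bonferroni does. If all 11 scores carry the planned effect, the probability that at least one stays significant is:

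| Assumed r | At least one significant after Holm |
|---|---|
| 0.3 | 96% |
| 0.5 | 91% |
| 0.7 | 82% |
| 0.8 | 77% |

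On average about 6.5 of the 11 remain significant.

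**Step 3: power with two primary scores.** The first Holm step is at 0.025.

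- 54 evaluable per group: 80% at 0.05 falls to 71% at 0.025.
- 146 recruited, 73 per group, 73 × 0.9 ≈ 66 evaluable: the expected statistic is 2.80 × √(66/54) = 3.10. Power is 87% at 0.05 and 80% at 0.025.

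**The case against.** Several points can fairly be made for the plan.

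- **The count of 11 is inferred.** The article lists two primary outcomes, and its sentence on the SF-36 describes what the instrument can yield, not a list of tests. A condensed article may leave the choice of score to a fuller document. This stands, and 11 must be labelled as a reading. It does not remove the point, because two scores at 0.05 each already give up to 9.75%, and the stated justification is wrong for any number of scores.
- **A reader might infer that a false finding of effectiveness is likely.** The figures do not support that. Over 11 scores the rate is at most 43%, and it counts results against the program. In the program's favour it is 24% at most under the assumptions used.
- **A reader might infer that any one subscale below 0.05 proves the hypothesis.** No section says so, and the Hypothesis section joins quality of life, function and pain with *and*. Equally, no section excludes it.
- **A reader might double the count for two follow-up visits.** The article specifies one repeated measures ANOVA per outcome, so separate tests per visit are not stated.
- **A reader might say that the second reason contradicts the plan's own sizing.** That is too strong. The article states no power, and it gives only an average effect over the SF-36 domains: "The pilot study SF-36 data showed an average improvement of 10 points across the eight domains measured". If only 3, 2 or 1 of the 11 scores carried a real effect (assumed 80% power each, r = 0.5), Bonferroni over 11 would miss all of them 26%, 35% or 51% of the time. The sentence is exaggerated and a poor reason, but it is not shown to contradict the sizing.
- **Non-adjustment is declared openly.** Readers can discount for it, but they cannot tell by how much while the decisive score is unnamed.

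**Conclusion.** The concern holds in a limited form. The article fixes separate unadjusted tests of two multi-score instruments, names no decisive score or time point, and defends this with two reasons that do not justify it.

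If all 11 scores are tested, the chance of at least one false positive is roughly 4 to 9 times the nominal 5% (18% to 43%, for r from 0.8 to 0). In the program's favour it is 9% to 24%, against 2.5%. With one score per instrument the two-sided rate is still up to about twice nominal. The results depend on the inferred count and on assumed correlations.

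The supported conclusion is that the error is substantially inflated and the decision rule undefined. It is not that a false claim of effectiveness is likely.

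**What to change.** 1. Under Primary outcomes, name one score per instrument and one time point. Choose them to match the stated aim, which includes pain: for example WOMAC pain or the WOMAC total, and one SF-36 score. Two function scores would leave pain out of the primary analysis.
2. Under Data Analysis, test the two by Holm at an overall two-sided 0.05. Report the remaining scores as secondary, with estimates and confidence intervals.
3. If all 11 scores must stay primary, apply Holm over the 11.
4. Delete the sentence that justifies not adjusting.

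**Cost.** The change is wording only. Assuming the sizing used 80% power, power per primary score at the 0.025 step is about 71% with 54 evaluable per group. With the 146 participants already planned (about 66 evaluable per group if 1:1 with 10% dropout) it is about 80%. Keeping all 11 primary costs more: at the first Holm step (0.05/11), power per score is about 49% with 54 per group and 60% with 66. Because the sizing rests on an average over eight SF-36 domains, the effect and SD assumed for the chosen SF-36 score should be stated.

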## Discussion

Self-management aims to motivate people to undertake the changes in behavior necessary to improve their lives. The preference of patients to actively manage their condition themselves is well matched to the aim of the multidisciplinary SM program to empower people to manage their condition [25]. People with OA of the knee have identified pain and problems with daily activities as the most important problems associated with their condition. Hence the results of the study will reflect their priorities. The outcome measures selected have demonstrated validity and are responsive within the range of change expected in response to the intervention.

This disease specific self-management program differs from other more generic arthritis programs. Using the skills and expertise of health professionals in a program providing disease specific education and self-management will provide a platform for behavior change that is not feasible with the limited knowledge base of lay leaders. The outcome measures are designed to reflect positive changes in pain, knee function and quality of life (intervention group), compared with those participants that are managed with conventional treatment (control group).

The study design compares the OAK program with the usual management of people with OA in the community. Randomisation to treatment or no treatment groups prevents conscious or unconscious bias [26]. Although blinding of group participants is not possible, the physiotherapists assessing outcome measures will be blinded to group allocation to minimize potential bias [27]. Using an intention to treat design will reflect the way the treatment will perform in the community and reduces the potential bias of drop out or non-compliant participants.

There is insufficient evidence to unequivocally claim that self-management is an effective treatment for osteoarthritis of the knee. The results of the study will provide evidence to guide clinicians and funding bodies to establish priorities regarding the provision of this disease specific program.
